### Ethical Considerations

The study protocol was approved by the Research Bioethics Committee of Universidad Santa María La Antigua (CBI-USMA; 2022-P004). Informed consent is read to participants via phone call. After verbal confirmation of acceptance to participate in the study, participants get a Google Forms link were they formally accept to be part of the study and attach an image of their personal sign. Once they finish filling the forms, they are assigned a unique code.

All data collected will be saved in a password-protected database. Only authorized research personnel will have access to this database. If a participant chooses to withdraw from the study, the data collected before their withdrawal will still be included in the analysis. Data collected on REDCap are identified with a specific number to protect the identity of the participant.

Some estimated harms that could be caused by this type of evaluations include fatigue, stress, or anxiety while either responding to the questionnaires or performing the neuropsychological tests. However, we expect minimal harm to our participants. If the participant needs it, the evaluation is rescheduled. Participants are informed that they are free to withdraw from the research study at any time. As exclusion criteria indicates eligibility for participating is based on participants not having a diagnosis of ADRD or other neurological disorders that affect cognitive functioning, all participants contacted and included in the study are cognitively healthy. Nevertheless, if a participant with a diagnosis of ADRD contacts the research team, researchers will refer them to a neurologist.

### Data Management

All data, including consent, will be added to a REDCap database that has all the measures obtained in this study. To ensure high-data quality collection, scoring of the tests is reviewed by 2 different evaluators at the end of the testing. This is done to improve interrater reliability in test scoring. All evaluators have been trained using the same tools and in a standardized environment to minimize variability in score interpretation. Test scoring instructions are followed precisely.

### Dissemination Policy

Results from this research will be published, shared, and presented at national and international conferences, science events, and high-impact journals. At the end of the study, participants will be given a summary of their results that will give them an insight of their cognitive status. The report will be divided in different cognitive domains, including “below average,” “average,” and “above average” to identify the participant’s cognitive level when compared with other peers of the same age range, sex, and education.

## Results

### Preliminary General Characteristics of the Sample

The demographic and clinical characteristics of the sample are summarized in Tables 1 and 2. Participants were mostly female (53/67, 79%) and were on average aged 62.2 (SD 7.6) years. Participants on average had 16.7 (SD 1.9) years of formal education. Most participants have a partner (44/67, 66%). Participants reported few cardiovascular, cerebrovascular, and psychiatric illnesses. Nevertheless, the most common chronic illness is hypertension (22/67, 33%), followed by hypercholesterolemia (19/67, 28%). Most participants identify as White (31/67, 46%) or other (20/67, 30%). Participants showed a high degree of functional independence in performing basic and instrumental activities of daily living. On average, participants had 1.5 (SD 1.8) symptoms of depression.

**Table 1 table1:** Protocol measures for teleneuropsychology assessment.

Measure			Description
**Screening measures**			
	TICS-M^a^	Measures domains such as orientation, verbal memory, attention, working memory, or abstraction and has no visual stimuli; cognitive impairment is established at ≤31 points	
	NACC^b^ Health History	Evaluates general health history, identifying potential neurodegenerative diseases or other risk factors that may disqualify participants in the research	
**Questionnaires**			
	NACC-Demographics Questionnaire	Addresses topics of age, sex, education, independence, type of housing, and civil status, among others.	
	GDS^c^	Consists of 30 yes or no questions completed via a REDCap^d^ form; if a participant scores >20 on the GDS, the study team enquires about suicidal ideation	
	The Functional Activity Index	Evaluates an individual’s ability to perform daily activities	
**Teleneuropsychological tests**			
	Montreal Cognitive Assessment	Cognitive screening tool that measures visuospatial skills, naming, verbal memory, working memory, attention, language, abstraction, and orientation	
	Craft Story Test	Short- and long-term verbal memory are measured with a related story	
	Rey Auditory Verbal Learning Test	Short- and long-term verbal memory are measured with a 15-word list	
	Benson Complex Figure	Short- and long-term visual memory and visuoconstruction are measured with a complex figure	
	Multilingual Naming Test	30-item test that measures naming ability	
	The Digit Span Test	Working memory and attention abilities are measured with series of numbers repeated in a forward and backward order	
	Verbal Fluency	Verbal phonological fluency is assessed by generating as many words as possible beginning with a specific letter (F, A, S, and M) in 1 min each	
	Category Fluency	Semantic fluency is assessed by generating as many words as possible from a specific category (animals, vegetables, and fruits) in 1 min each	
	Wisconsin Card Sorting Test-64	Executive function is measured by having the participant match cards according to certain rules (color, figure, and number of figures in card)	
	Boston Naming Test	15-item test that measures naming ability	
	Symbol Digit Modality Test	Speeded information processing is assessed by associating numbers with symbols as fast as possible in 90 seconds	
	Word Accentuation Test Chicago	Participants read a list of words and attempt to place the correct accentuation, measuring premorbid intelligence	
**Feasibility**			
	Teleneuropsychological Assessment Satisfaction Scale	Provides participants with an opportunity to give feedback on various aspects of the assessment, including satisfaction, the use of Zoom and REDCap, instructions, advantages, difficulties, recommendations, and overall time	

^a^TICS-M: modified Telephone Interview for Cognitive Status.

^b^NACC: National Alzheimer’s Coordinating Center.

^c^GDS: Geriatric Depression Scale.

^d^REDCap: Research Electronic Data Capture.

**Table 2 table2:** Demographic and clinical characteristics of the study participants (n=67).

Variable			Participants
Age (y), mean (SD)			62.2 (7.6)
**Sex, n (%)**			
	Female	53 (79.1)	
**Race, n (%)**			
	Afro-Panamanian or Black	11 (16.4)	
	Asian	1 (1.5)	
	Indigenous people	2 (3.0)	
	White	31 (46.3)	
	Unknown	2 (3.0)	
	Other	20 (29.9)	
**Marital status, n (%)**			
	Partnered	44 (65.7)	
	Not partnered	23 (34.3)	
Education (y), mean (SD)			16.7 (1.9)
Years smoking, mean (SD)			15.3 (12.4)
Age at smoking cessation (years), mean (SD)			36.7
Diabetes (yes), n (%)			6 (9)
Hypertension (yes), n (%)			22 (32.8)
Hypercholesterolemia (yes), n (%)			19 (28.4)
Thyroid disease (yes), n (%)			13 (19.4)
Arthritis (yes), n (%)			9 (13.4)
Number of cardiovascular disease, mean (SD)			0.25 (0.8)
Number of cerebrovascular illnesses, mean (SD)			0.15 (0.5)
Number of medical conditions, mean (SD)			1.1 (1.0)
Number of sleep-related illnesses, mean (SD)			0.33 (0.6)
Number of psychiatric diseases, mean (SD)			0.33 (0.8)
Depression (yes), n (%)			11 (16.4)
Anxiety (yes), n (%)			7 (10.4)
Geriatric depression symptoms, mean (SD)			1.5 (1.8)
Functionality Index, mean (SD)			0.5 (0.8)

### Expected Outcomes for Assessing Feasibility

Feasibility will be assessed based on an analysis of the tools, funding, expertise, and resources needed to conduct neuropsychological assessments. Likewise, the Teleneuropsychological Assessment Satisfaction Scale will assess feasibility through the satisfaction of the sample with the teleneuropsychology assessment. The Teleneuropsychological Assessment Satisfaction Scale provides participants with an opportunity to give feedback on various aspects of the assessment, including satisfaction, the use of Zoom and REDCap, instructions, advantages, difficulties, recommendations, and overall time.

So far, the Teleneuropsychological Assessment Satisfaction Scale (Multimedia Appendix 1) has shown that most participants (39/67, 58%) were very satisfied with the teleneuropsychological assessment, while high levels of satisfaction were found with other elements of the assessment, such as the use of the Zoom platform (47/67, 70%), the evaluator (57/67, 85%), or the REDCap platform (33/67, 49%). All participants reported instructions were clear. Most participants (49/67, 73%) were satisfied with being able to do the evaluation from home. Two-thirds of participants (44/67, 66%) reported that they were able to use electronic equipment, such as computers, phones, or tablets. Most participants (37/67, 55%) would recommend a teleneuropsychological assessment to others.

Although most of the sample (53/67, 79%) reported no difficulties at all, main limitations that were stated by participants were internet connection (8/67, 12%), space in which the assessment took place (8/67, 12%), and electronic equipment used (5/67, 7%). Other barriers (12/67, 18%) included the long duration of the assessment, confusing wording in questionnaires, problems with sound, interruptions, difficulties with the assessment materials, problems with the Zoom platform, availability for the assessment, lack of light, and complaints regarding their own abilities.

### Expected Outcomes for Creating Normative Data

In line with the FLOAT study [63], percentile ranks for each test’s raw scores will be calculated from cumulative frequency distributions and then normalized to a distribution with a mean of 10 and an SD of 3 (ie, scaled scores). These normalized scores will then be entered into a stepwise regression, including sex (male and female), education, and different age groups. Predictors contributing <5% of additional variance in the normalized scores will be retained for further regression-based adjustments.

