**Methods:**

This is a cross-sectional, descriptive, community-based study derived from the Development and Validation of Teleneuropsychology Normative Data for Older Adults in Florida (FLOAT) study. The study’s final sample will include 150 participants (aged ≥50 years). Participants will undergo initial screening to determine their eligibility and will be included if they have a basic understanding of and access to technological devices such as telephones, tablets, or computers; are free of cognitive impairment or serious health conditions; and provide informed consent. Participants will complete 2 questionnaires to determine if they can continue in the study. Participants who are eligible will be assessed with a teleneuropsychology cognitive battery and will answer questionnaires via a REDCap (Research Electronic Data Capture) link.

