### Statistical Analyses

Neuropsychological test results will be analyzed using multivariate statistical methods. We will perform initial data analyses with chi-square and ANOVA tests to observe distribution across age groups or other groups of interest. We will obtain raw scores of each test as well as composites of cognitive domains to conduct further analyses per test and per cognitive domain. Comparisons will be made regarding sex and age groups. Student *t* test will be applied to examine differences in performance between sexes and within age groups (the sample will be divided in 3 groups: aged 51-59 years, 60-69 years, and >70 years). Multivariable regression analyses will be performed to assess linear relationships between age, years of education, or other (ie, income) variables and cognition. Once we have assessed and ruled out potential interaction effects influencing participant performance, we will proceed with an in-depth analysis of normative data stratified by age, sex, and education level. Test scores will be standardized into *z* scores based on the mean and SD of the respective group, and these *z* scores will be subsequently converted into normative scores for each assessment. Cases with incomplete data will be excluded from analyses via listwise deletion.

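### The regression that makes the norms enters age in groups rather than in years, so everyone in a band gets one age correction and the cut-off drifts within the band

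*Protocol article*

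**What the plan says.** All places are in the protocol article.

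- *Expected Outcomes for Creating Normative Data*: raw scores become percentile ranks and then scaled scores with mean 10 and SD 3. Then: "These normalized scores will then be entered into a stepwise regression, including sex (male and female), education, and different age groups". The number and limits of the groups are not given there. The section says the method follows the FLOAT study. Its retention rule reads: "Predictors contributing <5% of additional variance in the normalized scores will be retained for further regression-based adjustments".
- *Statistical Analyses*, on association: "Multivariable regression analyses will be performed to assess linear relationships between age, years of education, or other (ie, income) variables and cognition".
- *Statistical Analyses*, in the sentence on *t* tests: "the sample will be divided in 3 groups: aged 51-59 years, 60-69 years, and >70 years". This is the only definition of age groups in the document.
- *Statistical Analyses*, on norms: "normative data stratified by age, sex, and education level", with z scores taken from the mean and SD of the respective group.
- *Dissemination Policy*: participants are told whether they are below average, average or above average, "compared with other peers of the same age range, sex, and education".

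No section enters age in years into the norms.

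**The concern.** One benefit of regression-based norms is that the age correction can change smoothly with age without splitting a small sample into cells. Entering age as groups gives that up. A person aged 60 and a person aged 69 receive the same correction, everyone in the open top band shares one, and the expected score steps at 60 and again at 70 with no change in performance.

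If performance falls with age, a fixed cut-off then flags too few healthy people at the young end of each band and too many at the old end. These norms feed the label returned to participants, so the chance of a below-average label would depend partly on where in the band a person sits. Grouping also discards some of the age variance before a rule based on explained variance decides which predictors stay.

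**Working it through.** The plan states no age effect, cut-off percentile or power, so there is no figure of its own to reproduce. The check asks how large the drift would be over a range of age effects.

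**Inputs from the article.** Mean age 62.2, SD 7.6 (n=67 so far); scaled-score SD 3; planned N=150; minimum age 50.

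**Assumptions.** Ages are truncated normal on 50–90, matched to that mean and SD and taken in whole years. The bands are 50–59, 60–69 and 70 or over. This closes the gaps the article leaves at exactly 50 and exactly 70, which are a separate matter. The age trend is linear. A low score is one below −1 SD, nominally 16%. The age R² is unknown, so 2%, 5% and 10% are shown.

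**Step 1: what the bands keep.** Band shares are about 43–44%, 40% and 16%, with mean ages of about 54.8, 64.0 and 74.3. Between-band variance divided by total age variance is 0.84, so about 16% of the age variance stays uncorrected inside bands.

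**Step 2: error left within a band.** Slope per year = 3 × √R² / 7.6. At R²=10% this is 3 × 0.316 / 7.6 = 0.125 points.
- Error at 60: 0.125 × (64.0 − 60) = +0.50.
- Error at 69: 0.125 × (64.0 − 69) = −0.62.
- Difference left uncorrected: 0.125 × 9 = 1.12 points, or 0.37 SD.
- Step at 60: 0.125 × (64.0 − 54.8) = 1.15 points.
- Step at 70: 0.125 × (74.3 − 64.0) = 1.29 points.

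**Step 3: share flagged.** True residual SD is s = 3 × √(1 − R²). The SD the banded norm would use is S = √(s² + slope² × 0.16 × 7.6²). With error d, the share flagged is Φ((−S − d)/s). At R²=10%, s = 2.846 and S = 2.871:
- Age 60: Φ((−2.871 − 0.50)/2.846) = Φ(−1.18) = 11.8%.
- Age 69: Φ((−2.871 + 0.62)/2.846) = Φ(−0.79) = 21.5%.

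| Age R² | Slope per year | Flagged at 60 | Flagged at 69 |
|---|---|---|---|
| 2% | 0.056 | 14.1% | 18.2% |
| 5% | 0.088 | 13.0% | 19.7% |
| 10% | 0.125 | 11.8% | 21.5% |

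In the open top band at R²=10%, the shares are 11.5% at 70 and 22.3% at 80. With age in years and a linear true trend, the share is the nominal 16% at every age.

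**Step 4: keeping age in the model.** This applies only if predictors adding at least 5% are meant to be kept. Banded age then needs a true R² of about 0.05 / 0.84 = 0.0595, roughly 6%, to show 5%. In simulation at N=150 and true R²=8%, with age as the only predictor, the observed R² reaches 5% in about 79% of samples with age in years and about 74–75% with three categories. The loss is small because two category terms also pick up a little more chance variance than one linear term.

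**The case against.** **The two regressions do not conflict.** One describes association and the other builds norms, and age may take a different form in each. A reader might infer a contradiction; the document does not support that. This objection stands.

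**Grouping is the document's consistent choice.** The objectives compare age groups, the norms are stratified by age, and the report promises comparison within an age range. Against that target a banded norm is right on average over the band. This stands as far as it goes, but it does not remove the uneven flagging within a band or the steps between bands, and no reason for grouping is given.

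**Three bands are carried over from the *t*-test sentence.** The norm section does not say how many groups it uses. This stands: narrower groups would shrink every figure above. Any grouping still gives one correction per group, and no other groups are defined.

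**The retention rule as printed keeps predictors adding less than 5%.** A reader might infer that banding makes age less likely to be kept. Under the printed rule the opposite holds, and an age effect of 10% would receive no age correction at all. The claim needs the inequality reversed, which is a separate error to resolve, and even then the loss is a few percentage points.

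**The drift depends on assumed values.** Neither the age R² nor the −1 SD cut is in the article, so quoting only the 10% row would overstate the case. At 2% the drift is modest.

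**This is a pilot with feasibility as a joint aim, and it already says reliable norms need a larger sample.** True, and it limits the weight of the point. It is no reason to leave a cheap improvement undone.

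**Conclusion.** The point holds as a suboptimal, stated analysis choice. The norm regression groups age, the only groups available are about a decade wide, and nothing elsewhere puts age in years into the norms.

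The consequence ranges from modest (about 4 percentage points between ages 60 and 69 if age explains 2% of variance) to nearly a doubling of the flagged share if it explains 10%. These figures rest on the assumed age distribution, three closed-up bands, a linear trend and a −1 SD cut. Under the retention rule as printed, a banded correction would be applied only when age adds less than 5%, so the top row of the table is the relevant one and the 5% row is the limit. If the rule is meant the other way, the 5% and 10% rows apply.

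The point does not invalidate the study, but it is worth settling before the final norms are produced.

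**What to change.** - In *Expected Outcomes for Creating Normative Data*, replace the age-group predictor with age in years as a continuous term. Check residuals against age and add a quadratic term if they show curvature.
- Keep the age bands for descriptive tables and for the planned group comparisons.
- In *Statistical Analyses*, align the stratified z-score norms with this model, and do the same for the same-age-range wording in *Dissemination Policy*. Otherwise the banding survives there. Look-up tables can be printed from the fitted model at chosen ages.
- Settle the direction of the 5% retention rule at the same time, since it decides when any age correction is applied.

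**Cost.** Wording only. Age is already collected in the demographics questionnaire, no participants are added, and recruitment stood at 67 of 150 in November 2024. The downsides are the assumption of a smooth age trend, which the residual check addresses, and tables that need a formula or finer age steps. The article does not show whether FLOAT groups age. If it does, a banded version may also be needed as a secondary table for the comparison with the US Hispanic sample.

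### As written, the 5% rule keeps weak demographic predictors and drops strong ones, leaving the regression-based norms uncorrected for the factors that matter

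*Protocol article*

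**What the plan says.** Under Expected Outcomes for Creating Normative Data, raw scores are turned into percentile ranks and then into scaled scores with mean 10 and SD 3. The next step reads: "These normalized scores will then be entered into a stepwise regression, including sex (male and female), education, and different age groups". The selection rule follows: "Predictors contributing <5% of additional variance in the normalized scores will be retained for further regression-based adjustments". The paragraph opens by saying that the approach follows the FLOAT study.

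Statistical Analyses describes another route to norms. Once interaction effects have been ruled out, "we will proceed with an in-depth analysis of normative data stratified by age, sex, and education level". There, z scores come from the mean and SD of the respective group and are then converted into normative scores. No variance threshold is used.

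Dissemination Policy promises each participant a report graded by cognitive domain, "to identify the participant’s cognitive level when compared with other peers of the same age range, sex, and education".

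**The concern.** A regression-based demographic adjustment exists to take out of a score the part that demographics explain. A variance threshold normally decides which factors explain enough to be worth removing. The printed rule does the reverse: it keeps the factors below the threshold, so those at or above it are not carried into the adjustment.

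If a test falls with age and age is dropped, older people are scored too low against their peers and younger people too high. The same holds for education or sex wherever either has a sizeable effect. That would defeat the comparison with demographic peers which the article sets out to provide, for every score produced by this route.

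**Working it through.** **Is the direction contradicted or explained elsewhere?** No. The 5% rule appears once. Statistical Analyses and Dissemination Policy both point to norms that account for age, sex and education, which is the opposite of what the rule does. A garbled symbol is unlikely, because the signs <, >, ≤ and ≥ come through as distinct characters elsewhere (Eligibility Criteria, Procedure, Questionnaires). The plan gives no figure to reproduce here; what is checked is a decision rule.

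**Inputs from the article.** Planned sample 150; scaled-score SD 3; mean age 62.2 years, SD 7.6 (Table 2, first 67 participants).

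**Input assumed.** The share of a test's variance explained by age, R². The article gives none. I take 15%, with a range of 5% to 30%, a linear effect, and scores that fall with age.

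**Mis-scoring of one older person when age is dropped.**
- Age 1.5 SD above the mean: 62.2 + 1.5 × 7.6 = 73.6 years.
- Shift in SD units = 1.5 × √R². Shift in points = 3 × 1.5 × √R².
- Share of healthy people of that age below a nominal 5th-percentile cut = Φ((−1.645 + 1.5√R²) / √(1 − R²)).

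| Assumed R² for age | Shift (SD) | Shift (points) | Share below the 5% cut |
|---|---|---|---|
| 5% | 0.34 | 1.0 | about 9% |
| 15% | 0.58 | 1.7 | Φ(−1.064/0.922) = Φ(−1.15), about 12% |
| 30% | 0.82 | 2.5 | about 16% |

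**How often the rule would drop or keep a predictor.** This was simulated with N = 150 and 4,000 runs per scenario, using rank-normalized scores (mean 10, SD 3), uncorrelated predictors, age and education as continuous variables, and all three predictors entered forward. Shares are assumed, in the order age/education/sex.

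| Assumed shares | Kept, rule as printed | Variance removed | Correlation of adjusted score with age* | Kept, rule reversed | Variance removed | Correlation with age* |
|---|---|---|---|---|---|---|
| 15/10/0% | 1% / 10% / 99.9% | 1% | 0.38 | 99% / 90% / 0.1% | 25% | 0.00 |
| 10/5/0% | 11% / 52% / 99.8% | 3% | 0.29 | 89% / 48% / 0.3% | 14% | 0.02 |
| 8/15/2% | 21% / 1% / 89% | 3% | 0.24 | 79% / 99% / 11% | 24% | 0.04 |

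*Average over runs; the sign depends only on how the predictor is coded.

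A predictor with a true 5% share is kept by the printed rule in 52% of runs. The 1.0-point lower end of the range therefore arises only about half the time.

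**What the kept predictors are.** A single null predictor reaches a 5% increment with probability 0.006 at N = 150 (0.069 at n = 67), so the printed rule would keep it more than 99% of the time (93% at n = 67) if it is in the model. However, an increment of about 2.6% is already significant at two-sided 0.05 with N = 150. Kept predictors adding between about 2.6% and 5% can therefore be real but small effects.

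**The case against.** The strongest reply is that this is a misprint which no analyst would follow. A single wrong sign, or 'retained' where 'removed' was meant, explains the sentence, and the article's stated purpose points the other way. That is probably right. It cannot be confirmed, because the FLOAT source is not at hand, and the printed rule is the only one given. A reader might infer that the investigators deliberately chose to adjust for weak factors; nothing in the article supports that.

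A second reply concerns scope, and it stands. A reader might infer that all of the study's norms would be uncorrected. The article does not support this: the z-score norms under Statistical Analyses are formed within age, sex and education groups without the 5% rule. The article does not say whether the regression-based norms replace or supplement them, so the harm can be claimed only for the regression-based set.

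A third reply also stands. It is tempting to say that the norms would be adjusted for noise. That is too strong, given the small real effects that fall below 5%. If the stepwise procedure also applies a significance test at entry, most null predictors would never enter the model, and what the rule then keeps would mainly be such small effects.

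Finally, the size rests on assumed variance shares. The education effect is especially uncertain, since education in the sample so far is narrow (mean 16.7 years, SD 1.9).

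**Conclusion.** The sentence is wrong as written and should be corrected. Applied literally, it leaves the regression-based norms uncorrected for demographic factors with sizeable effects and adjusts them only for weak or null ones. It is probably a slip, and it does not touch the group-based z-score norms.

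The illustrative size is about 1.7 scaled-score points for a person of about 73.6 years, and about 12% of healthy people of that age below a nominal 5% cut. Both figures assume that age explains 15% of the test's variance, that its effect is linear, and that the age distribution stays as in the first 67 participants. The conclusion about direction needs none of these assumptions.

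**What to change.** Replace the rule with wording such as: *A demographic predictor is kept for the regression-based adjustment if it adds at least 5% to the explained variance in the scaled score, and is dropped if it adds less.* Check that the analysis code applies the same direction.

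In the same revision, state how the regression-based norms relate to the stratified z-score norms under Statistical Analyses, and which set underlies the participant reports.

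The cost is one corrected sentence, one clarifying sentence and a code check. No data collection or recruitment is affected.
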